## Methods and design

### Study design

The current study is a randomized, controlled, multi-center, open label (no blinding) trial with two parallel groups. The study duration is 12 weeks, preceded by an enrolment period including pre-screening, informed consent, and definitive screening. A flow diagram of participants is shown in Fig. 1. If eligible, nursing home residents are randomly allocated into the control or test group directly upon screening (1:1 ratio). Nursing home residents in the control group will receive standard OD and nutritional care, and will be compared to residents in the test group receiving standard OD and nutritional care with extra daily supplementation of the test product. Measurements are performed at baseline (t_1_), 6 weeks (t_2_), and 12 weeks (t_3_). The schedule of enrolment, intervention and assessments can be found in Table 1.

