### Randomization

Eligible nursing home residents will randomly be allocated to the control or test group using the online randomization tool ALEA™ (ALEA Clinical by FormsVision, Abcoude, the Netherlands). Block randomization will be performed with 1:1 allocation based on nursing home (site) and type of resident (legally capacitated vs. legally incapacitated to act for oneself) and varying block sizes of two and four.

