### Study outcomes

The primary outcome of the DYNAMO study is the difference in body weight change between the control and test group from baseline to final measurements after 12 weeks of intervention.

Secondary outcomes are changes in nutritional intake, HRQoL, OD-specific QoL, and patient compliance to the test product. In addition, a food diary, oxygen saturation, blood nutrient and hydration markers, blood pressure, heart-rate, upper arm and calf circumference, Barthel Index, 7-day activPAL3™, activity log, rating of the test product and dysphagia severity will be assessed.

Any (serious) adverse events ([S]AEs) will be monitored, evaluated, and documented. The relation of (S) AEs to the test product will also be evaluated by a medical doctor. Specific safety outcomes of the current study are: respiratory tract infection, urinary tract infection, dehydration, pressure ulcer, fall incident, all-cause hospitalization, and choking. An overview of study outcomes, corresponding instruments and assessment details can be found in Table 5.

**Table 5 Tab5:** Overview of study outcomes, instruments, and assessment details

	***Outcome***	***Instruments***	***Score***	***Assessment details***
***Primary***	Body Weight	Calibrated lift with integrated scale, mobile chair with integrated scale or wheelchair platform with integrated scale	Body weight weighed to the nearest gram	The resident is in fasting state and preferably dressed in light clothing and without shoes
***Secondary***	Nutritional intake	Standardized three-day food diary and a kitchen scale	Food products weighed to the nearest gram	Food products, leftovers and napkins with spit out food pieces will be weighed by a member of the trained study team
	HRQoL and OD-specific QoL	Standardized questionnaire EQ-5D-5L [33] and VAS: EQ VAS, DSS, DHRQoL [34, 35] and DAS	EQ-5D descriptive system [no problems/slight problems/moderate problems/severe problems/extreme problems] EQ VAS [0–100 score], DSS [0–10 score], DHRQoL [0–10 score], DAS [0–10 score]	Self-assessment or proxy-assessment
	Compliance to test product	Standardized compliance log	Amount of product leftover [no leftover/quarter/half/three quarters/complete leftover]	Filled out by nursing staff
***Exploratory***	ADL	Validated Barthel Index (BI) [36]	0 [dependent] - 20 [independent]	Conducted by a member of the trained study team

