### Power calculation

Previous clinical trials on ONS in nursing home residents with malnutrition risk have shown a significantly increased body weight in residents that received ONS over a period of three to 6 months compared to residents receiving dietary recommendations or standard OD and nutritional care during this period [21–24]. In a large meta-analysis, Milne et al. (2009) [21] reported a significant weighted mean difference of 2.65% in body weight between patients with mixed geriatric conditions at risk of malnutrition using energy supplementation versus patients without energy supplementation. This equals an effect difference of ~ 1.4 kg for a person weighing 55 kg. This is in line with more recent studies reporting body weight change from baseline of 1.2 kg (SD 2.4) [24], 1.22 kg (SEM 0.45) [23], and 1.4 kg (SD 2.4) [39] after supplementation with ONS (500–600 kcal/day) for 8–12 weeks in nursing home residents with malnutrition risk. Therefore, an increase of 1.4 kg (SD 2.4) in body weight is assumed to be a reasonable expected mean outcome for the current test group. The mean body weight change for the control group is conservatively estimated to remain unchanged despite standard OD and nutritional care. Stange et al. (2013) [24] documented fourteen drop-outs from 87 residents (16%) in the test group. For the current study, we estimate a drop out percentage after randomization of 20%. Based on this a priori estimate with an alpha of 0.05 and 0.90 power, of the required sample size per group (control/ test) was made and totals 78.

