### Data analysis

SAS/STAT® Software (by SAS Institute, North Carolina, USA) will be used for analysis of the encrypted data. Descriptive statistics of numerical data will be presented using mean and standard deviation (SD) or median with interquartile range (IQR), and they will be checked visually for normality using histograms and Q-Q plots. Categorical data will be presented in terms of frequencies or percentages. Numerical data of compliance to the test product will also be dichotomized into compliant and not-compliant. Generally, all analyses will be performed according to the intention-to-treat (ITT) principle. Only residents compliant to the intervention will be included in the per protocol analysis, which will be used as a sensitivity analysis for the ITT analyses. Linear mixed models will be performed to check for differences in primary and secondary outcome parameters between the control and the test group at different time-points with correction for baseline differences. A linear mixed model analysis will be used, as this method uses all available data, deals with correlation between repeated measures and assumes missingness to be at random.

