Practical implementations and ethical considerations made it impossible to blind participants and assessors in this study. To the best of our knowledge, we have made every effort to limit the effects of this limitation. Participants are randomly allocated to a treatment arm and intervention procedures (apart from the intervention) are standardized for both treatment groups. The primary measure of the study is an objective and valid measure, all measurements are in line with standard care practice and possible effects will be considered in the analysis of the study outcomes.

This pragmatically controlled study closely reflects standard OD and nutritional care, and study outcomes therefore have real-life applicability. Execution of standard care in the study design also entails a number of limiting factors. Most importantly, standard care may differ slightly between nursing homes, and proper study execution is highly dependent on the engagement of all involved healthcare professionals. Both somatic and psychogeriatric nursing home residents will be included, since OD and malnutrition (risk) are common in both populations. This will result in a highly heterogeneous population, increasing outcome variability. In addition, including incapacitated residents limits some assessments or limits some assessments to be completed by a caretaker. A priori estimation of the inclusion rate is difficult, specifically, the informed consent rate, i.e. the willingness of residents or their legal representatives to participate. Hence, the inclusion rate will be closely monitored.

Dutch nursing homes often comprise of long-term somatic and psychogeriatric wards and short-term rehabilitation wards. Residents at rehabilitation wards follow a rehabilitation trajectory (e.g. after stroke). They are temporarily in need of high intensity care and leave the nursing home after a short period of time. Future studies could also target a group of rehabilitation residents with OD and concurrent malnutrition (risk). In addition, the body of literature on non-institutionalized older populations at risk for OD and malnutrition is poor.

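### Randomisation is stratified by nursing home and legal capacity, but the stated primary model names neither and leaves its baseline correction undefined

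*Protocol article*

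**What the plan says.** Three sections of the protocol article bear on this.

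- **Randomization:** "Block randomization will be performed with 1:1 allocation based on nursing home (site) and type of resident", the resident types being those with and without legal capacity, with "varying block sizes of two and four".
- **Data analysis:** linear mixed models are to test primary and secondary outcomes for differences "between the control and the test group at different time-points with correction for baseline differences". The reason given for the method is that it uses all available data, "deals with correlation between repeated measures and assumes missingness to be at random". No term for nursing home or legal capacity is named, fixed or random, and no covariate is listed.
- **Discussion:** among the limiting factors of a design built on usual care, "Most importantly, standard care may differ slightly between nursing homes".

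The primary outcome, under Study outcomes, is the "difference in body weight change between the control and test group from baseline to final measurements after 12 weeks" of intervention.

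**The concern.** Stratified blocks balance the arms within each home and capacity group. Differences between strata therefore largely cancel out of the treatment contrast. A model without the strata still counts that variation as residual error, so its standard error describes a less precise trial than the one that was run. The interval is then wider than it need be and some power is given up.

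The wording of the correction is a second, separate weakness. Read one way, it is ordinary adjustment for baseline weight. Read the other way, the covariates of the primary test depend on which variables look imbalanced once the data are in. The Blinding section says that the analysis cannot be blinded, so it is better that the text leaves no room for the second reading.

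**Working it through.** **1. The plan's own figure.** Inputs from the Power calculation section: "an increase of 1.4 kg (SD 2.4) in body weight is assumed" for the test group, no change in the control group, alpha 0.05, power 0.90 and 20% dropout. Two-sided testing is assumed; it reproduces the stated number.

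- n per arm = 2 × (1.960 + 1.282)² × 2.4² / 1.4² = 61.8, so 62.
- 62 / 0.80 = 77.5, so 78. This matches the article. No stratum term enters the calculation.

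**2. Effect of leaving the strata out.** Let R² be the share of variance in 12-week weight change explained by home and legal capacity. The documents give no value; 5% and 15% are assumed. The formulas treat balance within strata as perfect.

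- Unadjusted model SE = 2.4 × √(2/62) = 0.431 kg, whatever R² is.
- True sampling SD under stratified allocation = 0.431 × √(1 − R²).
- Ratio of the two = 1/√(1 − R²).
- Type I error = 2 × [1 − Φ(1.96 × ratio)].
- Unadjusted power = Φ((1.4 − 1.96 × 0.431) / true SD).
- Adjusted power = Φ(1.4 / true SD − 1.96).

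| R² (assumed) | True SD | SE too large by | Type I error, unadjusted | Power, unadjusted | Power, adjusted | Loss |
|---|---|---|---|---|---|---|
| 0 | 0.431 | 0% | 5.0% | 90.1% | 90.1% | 0 |
| 0.05 | 0.420 | 2.6% | 4.4% | 90.7% | 91.5% | 0.8 points |
| 0.15 | 0.397 | 8.5% | 3.4% | 91.9% | 94.1% | 2.2 points |

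**3. Check by simulation.** The setting was 124 analysed residents, stratified blocks of 2 and 4, SD 2.4 and 3,000 runs per scenario. Assumptions not in the documents: 10 homes, an equal split by legal capacity, complete 12-week change scores, and the variance shares. Each cell shows unadjusted, then adjusted.

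| Variance share, home + capacity | Mean SE (kg) | Type I error | Power at 1.4 kg |
|---|---|---|---|
| 0% + 0% | 0.430, 0.432 | 5.3%, 5.2% | 89%, 89% |
| 5% + 2% | 0.429, 0.417 | 4.2%, 5.1% | 90%, 91% |
| 10% + 5% | 0.429, 0.399 | 3.9%, 5.6% | 92%, 94% |
| 20% + 10% | 0.425, 0.361 | 2.4%, 5.0% | 94%, 97% |

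The Monte Carlo standard error at a 5% rate is √(0.05 × 0.95 / 3000) = 0.4 points, so the 5.6% is compatible with 5%. The simulation agrees with the formulas in direction and rough size. At a total share of 15% it puts the excess in the SE at 6 to 7% rather than 8.5%, which is plausible because unfinished blocks leave some imbalance within strata. The power difference runs from 0 to 3 points.

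**The case against.** The strongest reply is that the article gives the model a sentence or two and does not list its terms. Arm, visit and their interaction are not spelled out either, and nobody would conclude that they are absent. A reader might infer that the plan excludes the stratification factors. The documents do not say so, and a condensed article may leave the covariate list to a fuller document. This stands, and it limits the confidence of the point.

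A reader might also infer that covariates will be picked on observed imbalance by an unblinded coordinator. The article mentions no baseline testing, no threshold and no selection step. The Blinding section says the coordinator takes part in data analysis, not that this person chooses covariates. Adjustment for the outcome's own baseline value is at least as natural a reading.

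The Discussion says only that care may vary slightly between homes, and it ties heterogeneity to mixing somatic and psychogeriatric residents. Neither statement shows that home or legal capacity predicts weight change.

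Finally, setting adjusted power of about 91 to 94% against the planned 90% would overstate the gain. Stratification also raises the power of the unadjusted test, so the fair comparison is within the same design.

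What remains after all this is that the article does state an adjustment rule, that the rule has two meanings, and that followed literally it omits the strata.

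**Conclusion.** The point holds as a free improvement, with moderate confidence. The stated model does not name the factors that structured the randomisation, and its one adjustment phrase is ambiguous.

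If the strata are omitted, the error is on the cautious side. Under the assumed 5 to 15% share of variance, the consequences are a standard error about 3 to 8% too large, type I error of about 4.4 to 3.4%, and about 1 to 2 points of power forgone. With no stratum effect there is no loss. By these formulas the trial keeps at least its planned 90% power either way, and 78 per group stands.

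A reader might take a mismatch between randomisation and analysis to mean too many false positives. Omitting the strata does the opposite. The documents do not support any claim that the trial's conclusions would be anti-conservative for this reason, or that the intervals are certain to be wrong.

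**What to change.** Replace the baseline-correction phrase in Data analysis with a fixed list. The mixed model for each primary and secondary outcome would adjust for the baseline value of that outcome, legal capacity and nursing home. State that the arm contrast at 12 weeks is primary for body weight, and that no covariate is added or dropped because of observed imbalance.

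Nursing home can be a fixed effect or a random intercept. The choice depends on the number of homes, which the article does not give, and should be written down before analysis.

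The cost is wording only. Both factors are already recorded for randomisation, and neither data collection nor sample size changes. The article reports that inclusion was still to resume, so the text can be settled before any analysis. If the full protocol or SAP already lists these terms, confirming that is all that is needed.

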### State of the study

The study was initiated on the 22nd of August, 2019. The study will proceed with inclusion after Covid-19 and reopening of the centers.

## Discussion

Due to the impairment of oral intake and swallowing, residents with OD are more prone to becoming malnourished [13]. Nutrient density of solid food decreases as water is added to blend the food product, [40] which in turn could increase the feeling of satiety without sufficient caloric intake. In addition, nutrition intake is further hampered because texture modification of solid food products and thickening of liquids with thickening powder may affect appetite and patient compliance [18, 19]. Hence, providing best care for this specific group of patients requires an interdisciplinary approach. The search for available and appropriate nutritional care for dysphagic residents is still ongoing, and the need for tailored and practical solutions is becoming even more pressing due to the aging of the population [13].

The results of the DYNAMO study will help to enhance best care for nursing home residents with OD and malnutrition (risk). Best care encompasses the promotion of the safety and efficacy of swallowing and the optimization of the nutritional status. This study is the first study on the effect of pre-thickened ONS on nutritional status in a vulnerable group of nursing home residents with OD and malnutrition (risk).

We hypothesize that the test group will show an improved change of body weight compared to the control group after 12 weeks of intervention, based on results of previous studies with ONS supplementation in nursing home residents [21–24]. The effect is expected within a period of 12 weeks, meaning adjacent policy in care can be determined within this period. An extended study period will lead to unnecessary burden to the participants and a delay of the implementation of the intervention in standard care.

In addition, the previous studies were conducted in nursing home residents who did not specifically have OD and who were supplemented with regular ONS, i.e. not specifically designed and likely not suitable for residents with OD. Providing a pre-thickened ready-to-use amylase-resistant ONS with a consistency that suits the severity levels of OD could improve swallowing efficacy and safety and oral intake compliance in nursing home residents with OD and malnutrition (risk). This in turn could have positive effects on the nutritional status. The current study therefore also includes QoL, ADL, dietary intake, intake compliance to the test product, and other parameters related to nutritional status. Associations between these parameters will be assessed since improving nutritional status with ONS may further lead to improved QoL and ADL [41].

Practical implementation of the DYNAMO study was closely aligned with nursing home staff and experts in the field of OD and malnutrition. Assessment tools and measurements used in the current study are based on standard OD and nutritional care where possible. For example, SNAQ-RC was used for screening of malnutrition (risk) as this is the standard tool for residential care in the Netherlands. Dutch national OD guidelines recommend bedside screening assessments like a WST and a clinical observation of oral intake [16, 42]. Although the psychometric limitations of these methods are known, instrumental swallowing assessments with a higher sensitivity and specificity, i.e. videofluoroscopy of swallowing (VFS) or fiberoptic/flexible endoscopic evaluation of swallowing (FEES) [13], have practical limitations and are therefore not part of the standard nursing home care. In the current study, OD screening will be carried out using a combination of existing practice (WST/water thickness test and swallowing observation) and a simplified version of a validated evaluation of functional ingestive skills of older persons (MISA) in order to obtain a patient-tailored recommendation on the safest thickness level for liquids.

Practical implementations and ethical considerations made it impossible to blind participants and assessors in this study. To the best of our knowledge, we have made every effort to limit the effects of this limitation. Participants are randomly allocated to a treatment arm and intervention procedures (apart from the intervention) are standardized for both treatment groups. The primary measure of the study is an objective and valid measure, all measurements are in line with standard care practice and possible effects will be considered in the analysis of the study outcomes.

This pragmatically controlled study closely reflects standard OD and nutritional care, and study outcomes therefore have real-life applicability. Execution of standard care in the study design also entails a number of limiting factors. Most importantly, standard care may differ slightly between nursing homes, and proper study execution is highly dependent on the engagement of all involved healthcare professionals. Both somatic and psychogeriatric nursing home residents will be included, since OD and malnutrition (risk) are common in both populations. This will result in a highly heterogeneous population, increasing outcome variability. In addition, including incapacitated residents limits some assessments or limits some assessments to be completed by a caretaker. A priori estimation of the inclusion rate is difficult, specifically, the informed consent rate, i.e. the willingness of residents or their legal representatives to participate. Hence, the inclusion rate will be closely monitored.

Dutch nursing homes often comprise of long-term somatic and psychogeriatric wards and short-term rehabilitation wards. Residents at rehabilitation wards follow a rehabilitation trajectory (e.g. after stroke). They are temporarily in need of high intensity care and leave the nursing home after a short period of time. Future studies could also target a group of rehabilitation residents with OD and concurrent malnutrition (risk). In addition, the body of literature on non-institutionalized older populations at risk for OD and malnutrition is poor.

## Data Availability

Study datasets are available from the corresponding author upon reasonable request. By signing informed consent, residents or their legal representatives give permission to the study team to share encoded data with the subsidizing party. Study results will be published by the investigating party in a scientific journal.

## Abbreviations

AE: Adverse Events
BI: Barthel Index
BDA: British Dietetic Association
BMI: Body Mass Index
CTCM: Clinical Trial Centre Maastricht
DAS: Dysphagia related Anxiety Scale
DHRQoL: Dysphagia related HRQoL
DSS: Dysphagia Severity Scale
ESPEN: European Society for Clinical Nutrition and Metabolism
EQ-5D-5L: EuroQol 5-dimensions 5-level
EQ-VAS: EuroQol Visual Analog Scale
FEES: Fiberoptic Endoscopic Evaluation of Swallowing
GDPR: General Data Protection Regulation
HRQoL: Health-Related Quality of Life
IDDSI: International Dysphagia Diet Standardization Initiative
IQR: Interquartile Range
ITT: Intention-to-treat
ICH-GCP: International Conference on Harmonization Good Clinical Practice
METC: Medical Ethics Committee
MISA: McGill Ingestive Skills Assessment
NTR: Dutch (Nederlands) Trial Register
OD: Oropharyngeal Dysphagia
ONS: Oral Nutritional Supplementation
NUTRIM: School of Nutrition and Translational Research in Metabolism
SPIRIT: Standard Protocol Items: Recommendations for Interventional Trial
SLT: Speech and Language Therapist
SAE: Serious Adverse Event
SNAQ-RC: Short Nutritional Assessment Questionnaire for Residential Care
SD: Standard Deviation
V-VST: Volume-Viscosity Swallow Test
VFS: Videofluoroscopy
VAS: Visual Analog Scale
WST: Water Swallow Test
WMO: Dutch Act for Medical Research Involving Human Subjects
